# STATISTICAL ANALYSIS

# Descriptive statistics

**Power analysis**

Data on ablation rates.

Based on literature and local Dutch data the investigators agree that a mean ablation failure rate up to 10% is considered acceptable.

Definition of ablation success : A recent review has analyzed the success rate of ablation at 80% with 100mCurie after withdrawal.7 Results from Dutch centers vary from 88% , 93% and lower (68% and 86%) and 56%.13-15

A historical ablation success rate defined on the basis of the post therapeutic scan in those patient with a second blind I131 therapy will follow.

Event = ablation failure as defined above

Event =

ablation failure as defined above

Figure 1

*Background of the sequential design with stopping rule*

A sequential design with a stopping rule equipped with two boundaries, gives the opportunity to use every single consecutive ablative therapy in a daily executed interim analysis.(see fig.1)

The preset upper boundary allows premature stopping in case of an observed failure rate that is inferior to the acceptable rate of 10%, with a rate of 20% as alternative ( Total maximal number of patients 144; constant alpha=0.014, cumulative alpha=0.05; beta =0.10). This means that with a true failure rate of 10%, the probability of passing the upper boundary is below 5%, with a power of 90%.

The preset lower boundary allows premature stopping for futile testing (constant alpha=0.2638, cumulative beta=0.10; cumulative alpha=0.05). This means that with a true failure rate of 20%, the probability of passing the lower boundary is below 10% and that the probability of subsequent passage of the upper boundary would be below 5%.

The 50% probability of stopping (because of passing the upper or lower boundary) in case of a 20% failure rate is reached within the first 50 consecutive patients, whereas the 50% probability of stopping in case of a 10% failure rate is reached within 77 patients.

During the study, there is an analysis after entering each new patient. When the lower boundary is passed, sequential monitoring can be stopped, interim statistical analysis will be done and the use of rhTSH will become the standard treatment. Final statistical analysis will be done after completion of all 144 patients.

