When the upper boundary is passed, the study will be stopped prematurely and the use of rhTSH (with dosage and timing as in the protocol) can not become the standard treatment. Final statistics will be provided. Then two alternatives can be followed: withdrawal remains the standard treatment or a new study is started with different time and/or dosing of rhTSH.

The probabilities of stopping with various true failure rates are given in figure 2.

Figure 2 Probability of stopping at different failure rates 5 -25%

*Stopping rule with two boundaries*

*The upper boundary*

For one group of patients we can investigate inferiority of the failure rate p to H0: p<=p0 with the alternative H1:p>=p1. With a fully sequential design an upper boundary UB(n) can be constructed, being the maximally accepted number of events within n consecutive patients.

If the failure rate is p, then P(p,n-1,UB(n-1)) is the probability that the number of failures after (n-1) patients is UB(n-1). When the chosen one-sided level of significance is alpha(n-1), then P(p,n-1,Ub(n-1))>= alpha(n-1). Also alpha(n) has been chosen. In case an event occurs in patient n, there are two possibilities:

1) (P(p,n-1,UB(n-1)))*p=P(p,n,UB(n-1)+1)<alpha(n). This would mean that this result

is unacceptable, activating the stopping rule. Thus the upper boundary has been

passed, making UB(n-1)=UB(n). The probability of passage is P(p,n,UB(n)+1).

2) (P(p,n-1,UB(n-1)))*p=P(p,n,UB(n-1)+1)>=alpha(n). This would mean that this

result is acceptable, leaving the stopping rule inactivated. The upper boundary is

not passed, making UB(n)=UB(n-1)+1. The probability of passage is

P(p,n,UB(n)+1)=0.

The cumulative probability P(sum UB) to pass the upper boundary is the sum of P(p,n,UB(n)+1) from n=1 to n=N. N is the maximum of patients needed.

For p=p0 P(p0,sum UB) should not exceed a chosen value of alpha(rule). And for p=p1 P(p1,sum UB) should exceed a chosen value of (1-beta(rule)), being the power.

In this way the upper boundary serves as a fully sequential test of inferiority. When the boundary is passed, we do not accept H0 and declare the failure rate inferior to p0.

*The value of alpha(n).*

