1. With alpha(n) declining with rising n, as with the method of Pocock 16, the probability of "discordant" activation of the stopping rule is larger than with a constant alpha(n).17 Following the method of O'Brien en Fleming with a constant alpha(n)18, one would expect alpha(n)=alpha(rule)/N. This is not the case, because UB(n) is discrete in nature. Alpha(n) is larger than alpha(rule)/N. Z(1-alpha(n)) approximates Z(1-alpha(rule) +CTC. CTC is the socalled Christmas tree correction, which is approximatedly 0.583 in size.19

*The calculation of UB(n)*

Conventionally, UB(n) approximates n*p0+Z(1-alpha(n))*(n*p0)^0.5. Because of the discrete character of UB(n) this transforms into:

UB(n) = integer{n*p0 +Z(1-alpha(n)) *(n*p0)^0.5 +1}.

*The value of N*

The value of N can now be calculated as

N= integer{[Z(1-alpha(n)) *(p0)^0.5+Z(1-beta(N))*(p1)^0.5/(p1-p0)]^2+1}.

*The lower boundary*

*Futile testing*.

In a sequential design a stopping rule can be equipped with a lower boundary LB(n). Passage of that boundary would mean futile testing and monitoring could be stopped, accepting H0.

When constructed in such a way that UB(N)=LB(N), we know that the probability to pass the lower boundary would be 1-alpha(rule) in case p=p0 and (1-beta(rule)) in case p=p1, because of the limits set for UB(n).

Suppose the number of events after (n-1) patients equals LB(n-1) and LB(n)=LB(n-1)+1. If the failure rate is p1 and no events occur in patient n, then P(p1,n,LB(n))-1 is the probability that the number of failures after n patients is just 1 below LB(n). The overall probability to subsequently pass the upper boundary within the next (N-n) patients would be P(futile,n). P(futile,n)=0 in case LB(n)=LB(n-1). The sum P(p1, sum LB) of these probabilities P(futile,n) summed from n=1 to n=N we call alpha(futile). Alpha(futile) must be smaller than beta(rule).

Such a lower boundary can be approximated by:

LB(n)= integer{UB(N)+1-p1*(N-n)-Z(1-alpha1(n))*(p1*(N-n))^0.5)>=0. We choose alpha1(n) to be constant and with such a value that alpha(futile) is the result.

*Simultaneously active boundaries.*

The boundaries given above are still approximations. With low values of p0 and p1 the approximations do deviate from exact calculations. For this reason alone all probabilities should be calculated exactly. But there is a second reason to do so: the probability to pass one boundary is influenced by the probability to pass the other one.

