Such exact calculation can be done in a spread sheet programme. The calculations are repeated with changing values of the Z-parameters until the values of alpha(rule), (1-beta(rule)) and alpha(futile) meet the limits set.

Estimation of the failure rate p after activation of the stopping rule.

If a boundary is passed after k patients, with a total number of events of (UB(n)+1) for the upper boundary or of( LB(n)-1) for the lower boundary, p can be estimated.

When the true failure rate is p, then

a) After passing the upper boundary: the sum of (P(p,n,UB(n)+1) from n=1 to n=k is

0.5 for the estimation of p, whereas this sum is alpha(rule) for the upper limit of its

100*(1- 2*alpha(rule)) % confidence interval (CI) and 0.95 for the lower limit of this

CI.

b) After passing the lower boundary: the sum of (P(p,n,LB(n)-1) from n=1 to n=k is

0.5 for the estimation of p, whereas this sum is alpha(rule) for the lower limit of its

100*(1- 2*alpha(rule)) % confidence interval (CI) and 0.95 for the upper limit of this

CI.

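### The confidence limits for the failure rate after stopping are labelled the wrong way round for both boundaries

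*Protocol*

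**What the plan says.** The last part of the protocol's Statistical Analysis section explains how to estimate the failure rate p once a boundary has been passed after k patients. The quantity used is the probability, for a given true p, of passing that boundary at any patient from 1 to k. The point estimate is the p that makes this sum 0.5. The limits of a 100(1 − 2·alpha(rule))% interval, which is 90% with alpha(rule) = 0.05, are then assigned as follows:

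- Item a, upper boundary passed: "whereas this sum is alpha(rule) for the upper limit of its" interval, and the sum is 0.95 for the lower limit.
- Item b, lower boundary passed: "whereas this sum is alpha(rule) for the lower limit of its" interval, and the sum is 0.95 for the upper limit.

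The design these items belong to tests for a failure rate "inferior to the acceptable rate of 10%, with a rate of 20% as alternative", with at most 144 patients. The upper boundary has "constant alpha=0.014, cumulative alpha=0.05; beta =0.10" and the lower boundary "constant alpha=0.2638, cumulative beta=0.10; cumulative alpha=0.05".

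**The concern.** A confidence limit found by solving a tail probability for p depends on whether that probability rises or falls with p. More failures make an upper-boundary passage more likely and a lower-boundary passage less likely. The value 0.05 must therefore mark the low end of the interval after an upper-boundary stop and the high end after a lower-boundary stop. Items a and b say the opposite in both cases.

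This interval is the only method of estimation that the protocol sets out. Passing the lower boundary is meant to make rhTSH the standard treatment, and the natural question at that point is how high the failure rate could still be. Followed literally, the rule answers with the bottom of the interval.

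**Working it through.** **Direction from the protocol's own text.** The subsection on the upper boundary requires the cumulative probability of passing it to be no more than alpha(rule) at p0 = 10% and more than 1 − beta(rule) at p1 = 20%. With the stated values that is at most 0.05 at 10% and above 0.90 at 20%, so the sum rises with p. For the lower boundary, the background subsection puts the probability of passage below 10% when p = 20%. The subsection on that boundary puts it at 1 − alpha(rule) = 0.95 when p = 10%. So this sum falls with p. (The latter subsection gives 1 − beta(rule), not beta(rule), at 20%; even 0.90 would be a fall from 0.95.)

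**Inputs (Power analysis section).** p0 = 0.10, p1 = 0.20, N = 144, alpha(n) = 0.014 one-sided, alpha1(n) = 0.2638, alpha(rule) = 0.05. Hence Z(0.986) = 2.197 and Z(0.7362) = 0.632.

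**Boundaries as printed** (⌊ ⌋ is the integer part):

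- UB(n) = ⌊n·p0 + 2.197·√(n·p0) + 1⌋; stop when failures exceed UB(n).
- LB(n) = ⌊UB(N) + 1 − p1(N − n) − 0.632·√(p1(N − n))⌋, at least 0; stop when failures fall below LB(n).
- UB(144) = ⌊14.4 + 2.197 × 3.795 + 1⌋ = ⌊23.74⌋ = 23.
- UB(50) = ⌊5 + 2.197 × 2.236 + 1⌋ = ⌊10.91⌋ = 10, so an 11th failure at patient 50 passes the upper boundary.
- LB(81) = ⌊24 − 12.6 − 0.632 × 3.550⌋ = ⌊9.16⌋ = 9, so 8 failures at patient 81 pass the lower boundary (LB(80) = 8).
- LB(76) = ⌊24 − 13.6 − 0.632 × 3.688⌋ = ⌊8.07⌋ = 8, so 7 failures at patient 76 pass it.

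**Reproducing the design.** An exact patient-by-patient binomial recursion with both boundaries active gives:

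| Quantity | Protocol | Recomputed |
|---|---|---|
| Upper passage at p = 10% | below 0.05 | 0.0508 (0.0498 with alpha(n) = 0.0139, which rounds to 0.014) |
| Upper passage at p = 20% (power) | 0.90 | 0.899 |
| Lower passage at p = 20% | below 0.10 | 0.101 |
| 50% stopped, p = 20% | within 50 patients | 50 |
| 50% stopped, p = 10% | within 77 patients | 76 |

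The boundaries used here are therefore, to rounding, those of the protocol.

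**Solving for p.** F(p, k) is the sum of the passage probabilities from patient 1 to k for the boundary that was passed. Solving F(p, k) = 0.05, 0.5 and 0.95:

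| Stop | p at 0.05 | p at 0.5 (estimate) | p at 0.95 |
|---|---|---|---|
| Upper, k = 50, 11 failures | 0.109 | 0.199 | 0.305 |
| Lower, k = 76, 7 failures | 0.169 | 0.102 | 0.054 |
| Lower, k = 81, 8 failures | 0.175 | 0.108 | 0.060 |

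**Limits as labelled and as they should be:**

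| Stop | Estimate | Labelled lower / upper | Correct lower / upper |
|---|---|---|---|
| Upper, k = 50 | 19.9% | 30.5% / 10.9% | 10.9% / 30.5% |
| Lower, k = 76 | 10.2% | 16.9% / 5.4% | 5.4% / 16.9% |
| Lower, k = 81 | 10.8% | 17.5% / 6.0% | 6.0% / 17.5% |

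In each row the labelled upper limit lies below the estimate and the labelled lower limit above it. At every k examined the upper sum rose with p and the lower sum fell. Constructing the boundaries with a binomial variance, or omitting the + 1, changes the figures but not the reversal.

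**The case against.** The strongest reply is that only labels are wrong. The equations, the two solved values, the point estimate and the nominal 90% coverage are the same once the words are exchanged. The decision to stop rests on passing a boundary, and no criterion is placed on a confidence limit. An analyst who prints both limits beside the estimate would probably see that they are the wrong way round. The gaps quoted, such as 6.0% against 17.5%, are the two ends of one interval and would mislead only if one limit were used alone. The protocol also announces a final analysis after all 144 patients following a lower-boundary passage, and a statistical analysis plan that was not available may define other estimates.

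All of this is fair as to consequence: the error does not touch the operating characteristics, and it is easy to detect. It does not make the text right. The protocol states an explicit rule, the rule fails in the same way for both boundaries, and it contradicts the protocol's own requirement on the passage probabilities. The later analyses are mentioned but not described, so within this document nothing else supplies the interval.

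**Conclusion.** The concern holds. Items a and b both assign the limits in reverse. The error is certain from the direction of the passage probabilities and does not depend on the particular k. Its size, if one labelled limit is read alone, is the full width of the interval: 17.5 − 6.0 = 11.5 percentage points for a lower-boundary stop at patient 81, and 30.5 − 10.9 = 19.6 points for an upper-boundary stop at patient 50. These stopping points are illustrations. The figures assume the boundary formulas as printed, with alpha(n) = 0.014 and alpha1(n) = 0.2638 and both boundaries active. The text must be corrected before the rule is used, because after a lower-boundary stop it would present a rate well under the acceptable 10% as the upper limit when the upper limit lies much nearer the 20% alternative.

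**What to change.** Exchange the two labels in each item, and write 1 − alpha(rule) in place of the fixed 0.95 so that both ends follow from the same parameter:

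- Item a (upper boundary passed): the sum equals alpha(rule) at the lower limit and 1 − alpha(rule) at the upper limit.
- Item b (lower boundary passed): the sum equals alpha(rule) at the upper limit and 1 − alpha(rule) at the lower limit.

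Any spreadsheet already set up for these calculations should be checked for the same reversal. The cost is two sentences; the design, the sample size and the data collected do not change.

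### The near-side confidence limit after stopping uses a sum that includes patient k, so the stated 90% interval is too narrow on that side even once the limit labels are put right

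*Protocol*

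**What the plan says.** The rule stands in the Protocol, STATISTICAL ANALYSIS, Power analysis, in the closing part on estimating the failure rate once the stopping rule has been activated.

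- Item a: "After passing the upper boundary: the sum of (P(p,n,UB(n)+1) from n=1 to n=k is" equal to 0.5 for the estimate, with the same sum set to alpha(rule) and to 0.95 for the two limits.
- Item b: "After passing the lower boundary: the sum of (P(p,n,LB(n)-1) from n=1 to n=k is" then "0.5 for the estimation of p, whereas this sum is alpha(rule) for the lower limit of its" interval, with 0.95 for the other limit.

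The interval level is 100(1 - 2 alpha(rule))%, which is 90% with alpha(rule) = 0.05. All three values come from one sum that runs through k. No sum to k-1 appears.

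As printed, the limit labels are also reversed. The lower-passage sum falls as p rises, so 0.05 gives the larger p, yet that value is called the lower limit; item a has the mirror fault. That is a separate error. Everything below assumes the labels have been exchanged.

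**The concern.** A lower passage can occur only at certain values of n, and each carries a lump of probability. With such outcomes, each confidence limit counts the observed result in its own tail, so the two limits need different sums. Let S(k;p) be the probability of lower passage at or before patient k.

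- Upper limit after lower passage (far side): results at least as favourable as the one observed have probability S(k;p). Setting this to 0.05 is right.
- Lower limit after lower passage (near side): results at least as unfavourable as the one observed are all those that had not passed the lower boundary before k. Their probability is 1 - S(k-1;p). Setting this to 0.05 gives S(k-1;p) = 0.95, not S(k;p) = 0.95.

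Using S(k;p) for the near side leaves the observed result out of its own tail, so the lower limit is too high. After upper passage the upper limit is too low for the same reason. At stake is whether the reported interval has its stated 90% level. The rule is written out in the protocol, so it is not a detail left open for a later document.

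**Working it through.** **Inputs (Protocol, Power analysis).** p0 and p1: "acceptable rate of 10%, with a rate of 20% as alternative". Design constants: "Total maximal number of patients 144; constant alpha=0.014, cumulative alpha=0.05; beta =0.10". Lower boundary: "The preset lower boundary allows premature stopping for futile testing (constant alpha=0.2638, cumulative beta=0.10; cumulative alpha=0.05". Formulas: "UB(n) = integer{n*p0 +Z(1-alpha(n)) *(n*p0)^0.5 +1" and "LB(n)= integer{UB(N)+1-p1*(N-n)-Z(1-alpha1(n))*(p1*(N-n))^0.5)>=0". Z(1-0.014) = 2.197; Z(1-0.2638) = 0.632. Stop when events exceed UB(n) or fall below LB(n).

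**Boundaries.**
- UB(144) = int(14.4 + 2.197 × √14.4 + 1) = int(23.74) = 23.
- LB(43) = int(24 - 20.2 - 0.632 × √20.2) = int(0.96) = 0.
- LB(44) = int(24 - 20 - 0.632 × √20) = int(1.17) = 1. The first possible lower passage is 0 failures in 44.
- UB(3) = int(0.3 + 2.197 × √0.3 + 1) = int(2.50) = 2. The first possible upper passage is 3 failures in 3.
- Lower passage is possible at 24 values of n: 44, 48, 53, …, 144.

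**Reproducing the plan's figures.** An exact patient-by-patient recursion with both boundaries active gives alpha 0.0508 and power 0.899. It gives 50% stopped by patient 76 at p = 10% and by patient 50 at p = 20%. The plan states alpha below 5%, power 90%, and 50% stopped within 77 and 50 patients. For alpha(n) between 0.0135 and 0.0145, alpha runs from 0.0497 to 0.0515, so rounding of 0.014 explains the small excess.

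**Two cases by hand.**
- 0/44: S(44;p) = (1-p)^44. Setting this to 0.95, 0.5 and 0.05 gives p = 1 - 0.95^(1/44) = 0.12%, 1 - 0.5^(1/44) = 1.6% and 1 - 0.05^(1/44) = 6.6%. The interval 0.12% to 6.6% excludes the observed 0. No earlier lower passage is possible, so the near-side limit should be 0.
- 3/3: the upper-passage sum is p^3. Setting this to 0.95 gives an upper limit of 0.95^(1/3) = 98.3%, which excludes the observed 100%. It should be 1.

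**A typical stop near 10%.** For 7/76 the sum through k gives 5.4% to 16.9%. With the sum to k-1 for the near side it is 4.7% to 16.9%.

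**Error rates, summed over all possible stops:**

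| True rate | Lower limit above truth, sum through k | Same, near side to k-1 | Total coverage, sum through k |
|---|---|---|---|
| 1.5% | 16.1% | 4.5% | 83.9% |
| 3.25% | 11.6% | 5.0% | 88.4% |
| 4% | 9.9% | 4.9% | 90.1% |
| 7% | 7.0% | 4.8% | 88.9% |

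Coverage is a sawtooth in p, and 1.5%, 3.25% and 7% are low points. Between 2% and 40% the minimum is 86.8%, at 2.4%. Nearby values are 91.2% at 2%, 90.7% at 3%, 93.6% at 5% and 92.2% at 8%. With the sum to k-1 for the near side, coverage is at least 90.1% between 2% and 40%. At 10% and 20% it is 90.9% and 90.5% under either rule.

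**The case against.** **Limits on the reach of the error, which stand.** The protocol's own sources put ablation success between 56% and 93%, so failure between 7% and 44%; true rates of 1.5% to 4% lie below that. The extreme cases are rare: 0/44 has probability 0.93^44 = 4.1% at p = 7% and 0.90^44 = 1.0% at 10%. After lower passage the limit that bears on acceptability is the upper one, which is the same under both rules, and the error overstates failure. The protocol also calls the analysis at lower passage interim and places the final analysis after all 144 patients. The boundary points are not printed; they come from formulas that the protocol itself calls approximations.

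The last point does not rescue the rule. Other readings of the formulas put the first lower stop at 42 to 53, and 1 - 0.95^(1/m) then runs from 0.12% down to 0.10%, still above 0.

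**Stronger readings that a reader might infer, and that the documents do not support.**
- *The point estimate is also an error.* Setting the sum to 0.5 is a stated convention. It does pull the estimate up after lower passage: the mean is 5.8% at a true 5% and 10.8% at 10%. Giving the term at k half weight lowers this to 5.1% and 10.5%, but raises mean bias above about 14%: 24.0% against 23.4% at a true 20%, and 29.9% against 28.7% at 25%. That is a trade-off, not a correction.
- *23/144 by lower passage and 24/144 by upper passage should not share an estimate.* They give about 15.4% under either rule (15.42% and 15.45% with half weight). The cause is ordering results by stopping time, not including k.
- *The stopping decision is affected.* The boundaries decide, and they do not use the estimate or the interval. Which side of 10% the estimate for 7/76 falls on changes nothing.

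**Conclusion.** The point holds for the near-side limit only. The lower limit after lower passage and the upper limit after upper passage are solved from a sum that wrongly includes the term at k, so the interval does not hold its stated 90% level at low failure rates. After a typical lower stop the shift is modest (5.4% instead of 4.7% at 7/76); it is plainest at the first possible stops, where the interval excludes the observed proportion. The lower limit misses in about 7% to 16% of trials at the tabulated rates, against 5% nominal, and total coverage falls to 84%, 88% and 89% at 1.5%, 3.25% and 7%. Coverage at the two design rates, the upper limit after lower passage, and the stopping rule are untouched. This is a minor correction to reporting.

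The figures assume boundaries rebuilt from the printed formulas and constants, and exchanged limit labels. The direction of the error and the exclusion of 0 after a zero-event stop do not depend on the exact boundary points.

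**What to change.** In the estimation paragraph, once the labels are exchanged:

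- Far-side limit (upper after lower passage, lower after upper passage): keep the sum through k equal to alpha(rule).
- Near-side limit (lower after lower passage, upper after upper passage): solve the sum from n=1 to n=k-1 equal to 0.95. Where no earlier passage of that boundary is possible, set the limit to 0 after lower passage or 1 after upper passage.
- Point estimate: leave the 0.5 rule, and if wished add a sentence that it pulls the estimate up after lower passage. Half-weighting the term at k is an optional choice, with the trade-off described above.

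This costs two lines of text and one index in the spreadsheet. Boundaries, maximum sample size and conduct do not change. The downside is slightly wider intervals.
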